### Blinding

Participating GPs will be blinded in the sense that they are not informed about the study and the different interventions. Due to the use of routine health data, patients will not be aware of study participation and data collection. Statisticians will be blinded, but not study staff.

### Control group

GPs randomized to the control group will not be contacted or informed about the study. Hence, they will treat their patients as usual.

### Interventions

We test three interventions against the control group: (A) personalized feedback on own prescribing behavior in comparison to GPs of the region within a visual attention-grabbing graph (social norm feedback), (B) feedback like (A) plus an invitation to participate in the project’s own online training (eLearning) on rational prescribing practice and communication strategies, and (C) feedback like (A) plus an invitation to participate in an online peer-moderated training in quality circle format on the topic of rational antibiotic prescribing, communication strategies, and development of individual starting points for a sustainable behavior change. In detail, the interventions are designed as follows:*Group A* receives personalized, individual prescription feedback, which compares the GP’s prescription behavior relative to colleagues in the region. This is complemented by a simple but appealing graph of one’s own prescription quantity compared to the average prescription rate of peers in their region (social norm feedback). This shall encourage to critically question one’s own prescribing behavior.*Group B* receives personalized, individual prescription feedback as in (A), and in addition, an invitation to participate in a project-specific online training. The online training fulfills two requirements that initially seem contradictory. It must be generalizable and thus ensure broad application. At the same time, it must address the various causes of inadequate prescription practice. It is also known that for the group of high prescribers a “one fits all” approach cannot be effective since according to Rodgers they belong predominantly to the group of “late adopters” [14]. This apparent paradox for the design of the online training is resolved by a modularized intervention concept. The aim is to provide an individualized portfolio of relevant training modules for each participant in an automated way, which addresses, among other things, the main phenomena of non-rational prescription of antibiotics described in the literature. These include (a) dealing with unavoidable diagnostic uncertainty [15], (b) the mostly unfounded fear of making mistakes, (c) perceived prescribing pressure from patients [16, 17], (d) basic clinical misconceptions [18], (e) the use of treatment algorithms inappropriate to the setting (e.g., treatment regimens of hospital care applied to primary care), and (f) rational consideration of practice characteristics, such as a high proportion of particularly vulnerable patient groups (e.g., due to demographic characteristics, a high proportion of inpatient care facilities, or deprived population groups) [15]. Participating GPs undergo an initial assessment at the beginning of the online training. This assessment captures GPs’ attitudes and individual awareness of the problem of inappropriate antibiotic prescriptions. A pre-developed, weighted algorithm considers the respective information provided by the training participants and proposes an individually tailored module portfolio. For optimally addressing participants, the Transtheoretical Model of Behaviour Change (TTM) by Prochaska and Di Clemente is taken into account [19]. The TTM describes several stages on the way to a change in behavior. It originates from behavioral psychology and is used in interventions to change health behaviors, e.g., tobacco smoking and alcohol consumption, but also in changing medical (prescribing) behavior [20, 21]. The content of the modules focuses on knowledge transfer (e.g., guideline update, antibiotic substances), problem-solving strategies (e.g., doctor-patient communication, intercultural communication, safety netting), everyday strategies (e.g., medical documentation, integration of point-of-care tests, and delayed prescribing) and content that encourages reflection (e.g., evidence-based medicine, medical ethics). Depending on personal interest and recommended modules, the duration of the online training is estimated to range between 90 and 180 min (45 min minimum). If interested, participants can ask for information material to be sent to them afterwards.*Group C* receives personalized, individual prescription social norm feedback like (A), and in addition, the invitation to participate in a peer-moderated online training similar to quality circles. These peer-moderated trainings are each moderated by a GP colleague (peer), who already has experience in moderating quality circles. To prepare for the peer intervention, the peers undergo a specific online training. In the first part of the training, peers participate in online training on the intervention (B). In the second part, the peers are trained in three areas according to current medical-didactic findings [22, 23]: giving constructive feedback, motivational interviewing [24], and dealing with group dynamics in heterogeneous groups. The latter is also relevant regarding “difficult participants” in order to recognize and address resistance within the group. The trained peers then moderate the exchange with the participants in an online training and provide content of the individual modules according to their needs. Here, too, change management is to be initiated using TTM. For this purpose, the peer discusses value concepts as well as the individual problem awareness for inadequate antibiotic prescriptions within the group at the beginning of the event. The peer can thus focus and reflect on the intervention content according to the group specifics, both on the cognitive level and on the behavioral level.

Both, the online training and the peer-moderated online training will be CME (continuing medical education) accredited. Also, participants will receive an expense allowance. Overall, the intervention targets the entire group of patients treated by participating GPs for an illness that may involve the administration of an antibiotic.

### Harms

Harms are not expected as the careful prescription of antibiotics is based on national clinical guidelines.

### Outcomes

The primary outcome is the overall rate of antibiotic prescriptions, measured as the proportion of patients with antibiotic prescriptions out of all patients with prescriptions within the nine regional ASHIPs before intervention (October 2020–September 2022) and after it officially starts (October 2022–December 2023). All interventions are completed by December 2022. The changes in prescription rates between those two-time frames are compared between the control group and the interventions. Effects measured at this level are very robust, as neither imprecision in diagnosis coding (ICD 10) nor possible changes in coding behavior have an influence on this outcome. The same applies to the secondary outcomes. Secondary outcomes are the overall prescription rates before and after the intervention for cephalosporins and fluoroquinolones, respectively. The choice of these drug groups is based on the European Surveillance of Antimicrobial Consumption (ESAC) quality indicators for the outpatient sector [25] See Fig. 1.

**Fig. 1 Fig1:**
[figure not shown]
Schedule of enrolment, interventions, and assessments

### Sample size

We assume that a total antibiotic prescription rate of 12% (rate of high prescribers in the predecessor project RESIST, unpublished data) will be observed in the control group. This rate is expected to be reduced to 8.7% in group A, to 8% in group B, and to 7% in group C. Since all interventions shall be compared to the control, we adjust for multiple testing via the Bonferroni correction and hence the type 1 error is set to 1.67% (two-sided). A Poisson model was used for sample size calculation. To be able to show the effect assumed for the comparison between the control group and group A with a power of 80%, 2000 practices are required in both groups. Due to the feasibility, maximal 1250 practices can be included in group C for comparison to the control. Thereby a power of 98.8% can be gained. Group B consists of 2000 practices to include all remaining eligible practices in all nine participating regional ASHIP. For the comparison between the control group and group B, a power of 94.6% can be gained. This sample size calculation refers to the intention-to-treat (ITT) population. This population includes all randomized practices regardless of whether they accept the offer of training in groups B and C. However, we are also interested in the per-protocol (PP) population which is analyzed within a secondary analysis. The PP population includes only those practices in groups B and C that participated in the training courses according to protocol. Thus, only the assumed effects between the control group and groups B and C change. We assume that in group B, the rate in this population can be reduced to 7.5%. Furthermore, we assume a participation rate between 30% and 40%, i.e., between 580 and 800 practices participate in the online training. Assuming this difference and the Bonferroni adjusted type 1 error of 1.67 a power between 80% and 89% can be gained. In group C, we assume a participation rate between 17% and 20%, i.e., between 215 and 250 physicians will presumably participate in the peer-moderated online training. Under the assumption of a reduction to 6% and the Bonferroni adjusted type 1 error of 1.67 a power between 80% and 85.8% can be gained See Fig. 2.

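### Group C's assumed intention-to-treat rate of 7%, and hence its 98.8% power, does not fit the plan's own uptake and per-protocol assumptions unless decliners do far better than group A

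*Protocol article*

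**What the plan says.** All the figures are in the Sample size section of the protocol article.

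- Control rate: "We assume that a total antibiotic prescription rate of 12"%.
- Intervention rates: "This rate is expected to be reduced to 8.7% in group A, to 8% in group B, and to 7% in group C".
- Model: "A Poisson model was used for sample size calculation". The two-sided type 1 error is 1.67%, that is 5% divided by three.
- Stated powers against control: 80% for A (2000 v 2000), 94.6% for B (2000 v 2000) and 98.8% for C (1250 v 2000).
- Population: these powers are for intention-to-treat, and "This population includes all randomized practices regardless of whether they accept the offer of training in groups B and C".
- Participants in B: uptake of 30–40% (580–800 practices) and a rate of 7.5%.
- Participants in C: "In group C, we assume a participation rate between 17% and 20"% (215–250 physicians). Their rate is given by "Under the assumption of a reduction to 6"%.

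The Interventions section says that B and C receive the same kind of feedback as A, with an invitation to training added. The article gives no rate for practices in B or C that decline, and does not say how 8% and 7% were obtained.

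**The concern.** Under intention-to-treat, an arm's expected rate is the average over practices that train and practices that do not, weighted by uptake. In C about four practices in five are expected to decline. What they actually receive is A's feedback and an invitation they do not use, so A's 8.7% is the natural figure for them, and the only letter-only rate in the article. A minority at 6% mixed with a large majority near 8.7% should come out much closer to 8.7% than to 7%.

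The Statistical methods section makes the intention-to-treat analysis the only confirmatory one. The 7% is therefore the plan's statement of what the C v control comparison is expected to show, and the 98.8% is its claim about the chance of showing it. If the 7% is too optimistic on the plan's own inputs, the power claim is too. An observed rate near 8.2% in C could also be read as a disappointing result when it is about what the uptake assumptions predict.

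**Working it through.** **1. Reproduce the stated powers.** The calculation that fits is a Wald test of the difference of two Poisson rates with unpooled variance, counting each practice as one unit:

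power = Φ( |r₁ − r₂| / √(r₁/n₁ + r₂/n₂) − z ), with z = 2.394 for a two-sided 0.05/3.

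| Comparison with control (12%, n = 2000) | Rate | n | Computed | Stated |
|---|---|---|---|---|
| A | 8.7% | 2000 | 80.2% | 80% |
| B | 8% | 2000 | 94.6% | 94.6% |
| C | 7% | 1250 | 98.8% | 98.8% |
| B per-protocol | 7.5% | 580 / 800 | 81.0% / 89.2% | 80% / 89% |
| C per-protocol | 6% | 215 / 250 | 80.6% / 85.8% | 80% / 85.8% |

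For C: 0.05 / √(0.12/2000 + 0.07/1250) = 0.05 / 0.01077 = 4.642, and Φ(4.642 − 2.394) = 98.8%. All seven figures reproduce to within about one point, so the power arithmetic is right for its inputs. The question is about the inputs.

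**2. Expected intention-to-treat rate in C.** Rate = uptake × participant rate + (1 − uptake) × decliner rate, with decliners at 8.7%. That 8.7% is an assumption drawn from the Interventions section.

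- 17% uptake: 0.17 × 6 + 0.83 × 8.7 = 8.24%
- 20% uptake: 0.20 × 6 + 0.80 × 8.7 = 8.16%

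**3. Power for C at those rates**, by the formula in step 1:

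- 8.24%: 0.0376 / 0.01122 = 3.350, power 83.0%
- 8.16%: 0.0384 / 0.01119 = 3.431, power 85.0%

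Other common variance forms (pooled difference, log rate ratio, square root, two proportions) give 78.7–87.6% for C. None of them reproduces the full set of stated powers.

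**4. What would make 7% right in C**, changing one input at a time:

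- Decliner rate: (7 − 0.17 × 6)/0.83 = 7.20%, or (7 − 0.20 × 6)/0.80 = 7.25%. That is about 1.5 points below A, and below the 7.5% assumed for practices that complete B's training.
- Participant rate: 8.7 − 1.7/0.17 = −1.3%, or 8.7 − 1.7/0.20 = 0.2%, against the stated 6%.
- Uptake: (8.7 − 7)/(8.7 − 6) = 63%, against the stated 17–20%.

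**5. Could selection explain it?** Suppose the invitation has no effect and decliners sit at 7.20–7.25% simply because they are different practices. For the letter-only average to remain 8.7%, those who accept would have had a letter-only rate of (8.7 − 0.83 × 7.205)/0.17 = 16.0%, or (8.7 − 0.80 × 7.25)/0.20 = 14.5%. Both exceed the 12% assumed for control.

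**6. The same check for B.**

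- 30% uptake: 0.30 × 7.5 + 0.70 × 8.7 = 8.34%, power 89.2%
- 40% uptake: 0.40 × 7.5 + 0.60 × 8.7 = 8.22%, power 91.4%

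Reaching 8% needs decliners at (8 − 0.30 × 7.5)/0.70 = 8.21% to (8 − 0.40 × 7.5)/0.60 = 8.33%. Through selection alone it needs a letter-only rate of about 9.3–9.8% among those who accept. Neither is far-fetched.

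**The case against.** The strongest objection is that the article never gives a decliner rate, so the 8.7% is supplied by the reader. The intention-to-treat question is the effect of offering training, and the invitation is part of that offer. It might do something even when declined. The 8.7% is also an average over practices that would and would not have accepted, so decliners need not match it. This stands as a limit on the wording. A reader might infer that 7% is arithmetically impossible, but the documents support only that it is unreconciled with the other figures. The objection does not explain C, because the invitation effect or selection needed there (steps 4 and 5) is large and nowhere stated.

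For B the objection succeeds. The gap is 0.22–0.34 points, 8.22–8.34% rounds to 8%, and a modest invitation effect or some selection would close it. A reader might infer that B's rate is contradicted as well; the figures do not show that.

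It is also fair to say that no design decision rests on these powers. The 2000 per group comes from A v control at 80% power, C's 1250 is set by feasibility, and B takes the remaining eligible practices. B v C and C v A are not among the confirmatory comparisons and carry no power claim, so a smaller expected gap between those arms undermines no stated power for them.

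Finally, an article may leave the derivation of such rates to the full protocol. That excuses the missing derivation. It does not remove the tension between figures printed in the same paragraph.

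**Conclusion.** The point holds for group C. Given 17–20% uptake, 6% in participants and decliners responding as group A, the expected intention-to-treat rate is 8.16–8.24%, about 1.2 points above the stated 7%. Power against control is 83.0–85.0%, about 14–16 points below the stated 98.8%. This rests on the 8.7% for decliners, which is an inference from what they receive, and on the plan's own power method, which treats each practice as one Poisson unit. Absolute power would also depend on patients per practice and overdispersion, which this check does not address.

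B's figures (8.22–8.34% and 89.2–91.4%, against 8% and 94.6%) are a remark only.

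A reader might infer that the trial is underpowered. That is not shown: on the plan's method both recomputed powers stay above 80%. The point is an inconsistency between assumptions that makes one stated confirmatory power too favourable. It should be corrected, but it ranks below a must-fix.

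**What to change.** In the Sample size section, state the rate assumed for practices in C that do not take up training. Derive C's intention-to-treat rate from uptake, participant rate and that non-participant rate, and restate the power against control. With non-participants at 8.7%, this is a rate of 8.16–8.24% and a power of about 83–85% on the present method. Alternatively, keep 7% and justify the non-participant rate of about 7.2% that it requires. For consistency, derive B's rate in the same way.

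The cost is a few sentences and a less favourable power figure for C. Sample sizes, randomisation and conduct do not change.

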### Statistical methods

All prescription rates for the primary and secondary outcomes are presented descriptively for the entire sample and separately according to groups. Sampling units are practices. A negative binomial regression model will be used to evaluate whether the change of prescription rates differs between control and intervention(s) (primary outcome). The negative binomial model is used because we assume that the mean and variance for prescription rates will be different (also seen in the RESIST study). Hereby, the number of antibiotic prescriptions after the intervention(s) is considered as the dependent variable, the number of patients is treated as the offset variable, the grouping variable and the area of the respective regional ASHIP are fixed effects, and the rate before the introduction of the intervention(s) is a covariate in the model. Although we used the Bonferroni-corrected significance level within the sample size calculation, we will evaluate the primary outcome with the less conservative Dunnett test which uses the information that the three interventions will be compared to the same control. The resulting adjusted *p* values will be compared to the global significance level of 5%.

The secondary outcomes will be exploratively analyzed using a negative binomial model without adjustment for multiple testing. Thereby, the dependent variables are the prescription rates for cephalosporins and fluoroquinolones, respectively. The fixed effects are the grouping variable, the area of the respective regional ASHIP, and the rate before the introduction of the intervention(s) for cephalosporins and fluoroquinolones, respectively. The number of patients serves as the offset variable.

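### The stated powers come from a Poisson formula that gives each practice the exposure of a single patient; they understate the trial's power, and the claim that 2000 practices are required is unsupported

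*Protocol article*

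**What the plan says.** The Sample size section assumes an antibiotic prescription rate of 12% under control and says: "This rate is expected to be reduced to 8.7% in group A, to 8% in group B, and to 7% in group C". The two-sided type 1 error is 1.67% after Bonferroni correction. The method is given in one sentence: "A Poisson model was used for sample size calculation". For control versus group A the section concludes that "with a power of 80%, 2000 practices are required in both groups". It then gives 94.6% for B (2000 practices) and 98.8% for C (1250 practices). The per-protocol figures are 80% to 89% for B (580 to 800 practices, rate 7.5%) and 80% to 85.8% for C (215 to 250, rate 6%). No number of patients per practice and no between-practice variation is stated.

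The Outcomes section defines the primary outcome as the proportion of patients with an antibiotic prescription among all patients with a prescription. The Statistical methods section makes practices the sampling units and plans a negative binomial regression with the number of patients as offset and the pre-intervention rate as covariate. Its reason is: "The negative binomial model is used because we assume that the mean and variance for prescription rates will be different".

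**The concern.** Each practice treats many patients, so its rate carries far more information than one patient's outcome. Practices also differ from one another, which takes some of that information away. A power calculation for this design needs both quantities, and the one reported appears to use neither. It also rests on the Poisson assumption that the analysis section sets aside.

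At stake are every power figure in the article and the only stated reason for putting 2000 practices in group A and in the control group. The published figures also suggest that the trial can just detect a fall from 12% to 8.7% (rate ratio 0.087/0.12 = 0.725), when it could detect much smaller changes.

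**Working it through.** **1. Reproducing the stated powers.** The rates, numbers of practices and alpha are those of the Sample size section. With alpha = 0.05/3 two-sided, z = 2.394. The formula is the unpooled Poisson rate difference with exposure 1 per practice:

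power = Φ( (p0 − p1) / √(p0/n0 + p1/n1) − 2.394 ), with p0 = 0.12 and n0 = 2000.

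For A: SE = √(0.12/2000 + 0.087/2000) = 0.010173; 0.033/0.010173 = 3.244; Φ(3.244 − 2.394) = Φ(0.850) = 80.2%.

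| Comparison with control | n1 | p1 | Recomputed | Stated |
|---|---|---|---|---|
| A | 2000 | 0.087 | 80.2% | 80% |
| B | 2000 | 0.08 | 94.6% | 94.6% |
| C | 1250 | 0.07 | 98.8% | 98.8% |
| B per protocol | 580 | 0.075 | 81.0% | 80% |
| B per protocol | 800 | 0.075 | 89.2% | 89% |
| C per protocol | 215 | 0.06 | 80.6% | 80% |
| C per protocol | 250 | 0.06 | 85.8% | 85.8% |

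Solving the same formula for 80% power in A gives (2.394 + 0.842)² × (0.12 + 0.087)/0.033² = 1990 practices per group, against the stated 2000.

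Other forms were tried: log rate ratio, pooled score, Poisson-regression null variance, square-root transform, two proportions, and a larger alpha. None matched all seven figures within two points. For example, the log rate ratio with exposure 1 gives 79.8% for A but 67.7% for B per protocol at 580 practices and 51.3% for C per protocol at 215.

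The article does not state the exposure, but the match fixes it at one per practice. The control group is then credited with 2000 × 0.12 = 240 events and group A with 2000 × 0.087 = 174.

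**2. Could this be a hidden allowance for clustering?** The formula gives one control practice's rate a variance of 0.12. A proportion with mean 0.12 can have a variance of at most 0.12 × 0.88 = 0.1056, reached only if every practice prescribes antibiotics to all or none of its patients. Using p(1 − p) in both groups, for a comparison of unweighted practice rates:

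- A: 0.033/0.009618 = 3.431, power 85.0%
- B: 0.04/0.009466 = 4.226, power 96.7%
- C: 0.05/0.010241 = 4.882, power 99.4%

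So even the most extreme clustering possible for a proportion leaves power above the stated figures.

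**3. Power with patients and overdispersion included.** The article gives neither patients per practice (m) nor the between-practice coefficient of variation (CV). Assumed ranges: m = 200 to 2000, CV = 0.2 to 1.0. With dispersion k = CV²:

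SE²(log rate ratio) = (1/n0)(k + 1/(m·p0)) + (1/n1)(k + 1/(m·p1)).

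Least favourable corner, A versus control, m = 200, CV = 1.0: SE² = (1 + 1/24)/2000 + (1 + 1/17.4)/2000, so SE = 0.0324. Then ln(0.12/0.087) = 0.3216; 0.3216/0.0324 − 2.394 = 7.53, which is power above 99.9%. Over the whole grid, power exceeds 99.9% for all three comparisons.

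The rate ratio detectable with 80% power for A versus control runs from 0.90 (m = 200, CV 1.0; 12% to 10.8%) to 0.98 (m = 2000, CV 0.2; 12% to 11.7%).

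To bring power for A down to 80% at m = 200 to 2000, k would have to be about 9.8 to 9.9, a CV of about 3.1.

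**The case against.** The strongest reply is that the error does no harm. It understates power, so the trial is safer than advertised. The test, the type 1 error, the intention-to-treat set and the estimates do not depend on it. The sizes of B and C have other stated reasons: all remaining eligible practices for B, and for C feasibility ("maximal 1250 practices can be included in group C for comparison to the control"). The interventions are letters and training offers, and the endpoint comes from routine claims, so extra practices cost little. All of this stands, and it limits the point to correcting the figures and the justification.

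Two technical objections also stand in part. First, the variance ceiling in step 2 applies to the proportion defined under Outcomes. The Statistical methods section models a number of prescriptions, which can exceed one per patient, so the ceiling does not strictly bind there. This does not rescue the calculation, given the dispersion shown at the end of step 3. Second, the formula in step 3 is simpler than the planned analysis: it omits the baseline-rate covariate and region, uses one common practice size, and keeps Bonferroni where the analysis plans Dunnett. Its results are scenarios, not the trial's power.

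A reader might also infer more than the article supports:

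- **That the trial is underpowered because clustering was ignored.** The calculation points the other way.
- **That a significant result would mislead about effect size.** Significance never implies the planned effect, and the article commits to rate ratios with 95% confidence intervals.
- **That comparisons between intervention arms should be added.** The confirmatory family is each intervention against control, and nothing here shows that choice to be wrong.

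**Conclusion.** The point holds as an error in the reported power figures and in the justification of sample size. That the stated powers use one unit of exposure per practice rests on the article's own inputs and on a match to all seven figures. It conflicts with both the outcome definition and the planned model. The stated 80%, 94.6% and 98.8%, the per-protocol ranges and the need for 2000 practices are therefore wrong as written.

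The direction is conservative. The gain of 0.6 to 5 percentage points in step 2 needs no outside figure, only that the outcome is a proportion. The figures in step 3 depend on the assumed practice sizes and variation, and the exact values need the investigators' data. The primary analysis remains valid, and the group sizes need not change.

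**What to change.** Keep the group sizes and replace the power statements in the Sample size section:

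- Give power and the detectable rate ratio for each comparison under a negative binomial model.
- Take patients per practice and dispersion from T0 or RESIST data, preferably the residual dispersion after adjusting for the baseline rate, and report the values used.
- State which alpha adjustment the calculation uses, since the Sample size section uses Bonferroni and the analysis uses Dunnett.
- Recompute the per-protocol figures in the same way.
- Delete the claim that 2000 practices are required for 80% power, and justify the sizes of group A and control by availability or by the smaller effect that can be detected.

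The cost is one calculation from data already held and a rewritten paragraph. No practices are added and the analysis does not change.
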